**ABSTRACT**

**Background:** Carcinoma of the cervix is the most prevalent gynaecological malignancy in our environment, and it is associated with significant morbidity and mortality. Papanicolaou test is a well-recognised and efficient screening modality but the uptake of Pap smear in our environment remains poor. Fear of pain from speculum insertion during vaginal examination has been noted as a factor that may reduce the compliance of women to cervical cancer screening and repeat testing. Speculum lubrication may help to reduce these pain and discomfort, but there are fears of its interference with cytological results.

**Aim and Objectives:** To determine and compare adequacy of cervical cytology smears and mean pain scores of women undergoing cervical screening with or without speculum lubrication.

**Research Methodology:** This proposed work will be a randomized controlled study among women having cervical cancer screening at the gynaecological clinic of Nnamdi Azikiwe University Teaching Hospital, Nnewi. Sixty-six patients would be randomly assigned to the ‘Gel group’ and another 66 patients to the ‘No Gel’ group. Samples will be collected from each participant for Pap smear with lubricated vaginal speculum for the ‘Gel group’ and non-lubricated vaginal speculum for the ‘No Gel group’. Pain scores will be assessed with the numeric rating scale for pain. The primary outcome measures will be the mean numeric rating scale pain scores and proportion of women with inadequate cervical cytology smears.

**Handling of Results:** The Statistical Packages for Social Sciences (SPSS) would be employed for data analysis. Statistical test of significance would be deduced at p-value less than 0.05.

**Strengths and Limitations: T**his proposed study is the first of its kind in Nigeria. Conclusions may not be generalized to other types of lubricant gels since only one type of lubricant gel will be used. The histopathologist and the study participants will be blinded hence double-blind.

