Water soluble lubricant gels are other options for speculum lubrication and have been shown to be more effective than water. In the United States of America (USA), Hill et al in their study in 2012 randomized 120 women into two groups. One group had before insertion, application of 3mls of water to a plastic speculum and the other group had 0.3ml of gel applied to the speculum before insertion. The women were not aware of their intervention arm placement and were told to state their intensity of pain on a 0 to 10 visual analogue scale (VAS) following speculum opening. Significantly lesser pain was documented for women in the gel intervention arm compared to that of water. (Mean scores 1.4 versus 2.2) Also, more scores of ‘0’ were documented in the gel intervention arm. (34% versus 10%).^30^

Topical analgesic containing lubricant gels can also be used to lubricate the speculum during vaginal examinations. In 2012, Keskin et al demonstrated in their study in Turkey that topical analgesic containing lubricant gel is more effective than water soluble lubricant gel in reducing pain and discomfort during vaginal examinations. In this study the women were placed at random to an EMLA (lidocaine-prilocaine) arm, lubricating gel arm and a control arm. Using the VAS scale the women were told to state their level of pain at insertion, during opening and following removal of speculum. Women in the EMLA group recorded significantly lower pain values at all stages of speculum use than their counterparts in the lubricant gel arm and control arm (P<0.001) while women in the gel arm recorded lower pain values compared to their counterparts in the control group except in the second phase of the procedure. P<0.001. ^31^

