Purposive sampling approach will be employed. Following informed consent, selected women will be assigned at random into two arms, namely the gel group and no gel group with the aid of computer created sporadic numbers. The sequence of randomization will be generated by tfhe computer via randomly permuted blocks (blocks of 4, allocation ratio 1:1). An independent person will perform the randomization and will not be involved in the study. The independent person will create a randomization table using computer software program available at <http://mahmoodsaghaei.tripod.com/Softwares/randalloc.html>. Serially numbered opaque sealed envelopes will be used for allocation concealment. The study interventions would be printed in a sheet of paper put in serially numbered opaque closed envelopes. The envelopes would be kept and opened by an independent person. Once the envelope is opened the allocation of the participant would not be changed. Each of the envelopes will contain either a sheet of paper showing gel group (Group A) placing the patient into the group using the speculum lubrication or a paper displaying no gel group (group B) placing the patient into the group receiving dry speculum (without speculum lubrication). Participants cannot be switched from one group to the other once they are placed in a group.

4.10 **STUDY PROCEDURE**

The consent for Pap smear will be gotten for each person during the visit. After explaining the procedure, the woman will be placed in dorsal position with the legs flexed at the knee and adducted at the hips.

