The vial will then be taken to the histopathology laboratory of Nnamdi Azikiwe University Teaching Hospital, Nnewi where it would be transferred into a centrifuge tube with same quantity of cleaning solution. The fluid will then be centrifuged for 10 minutes at 1400 rpm; the supernatant will be removed. Smears will be made from the sediments after mixing with the cellular base solution (Diapath S.p.A Martinego, Italy) and stained by the Papanicolaou staining method and reported using the Bethesda system stating whether the sample is satisfactory or not and the reason for unsatisfactory results. Samples will be recorded as “unsatisfactory” if no endocervical cells are present, if they are obscured by blood, or if drying artifact or gel overlay are present; otherwise, they will be recorded as “satisfactory”. ^19^ The histopathologist will not be aware of the intervention arm (group of patients) to which the smears to be analysed belong.

4.11 **OUTCOME MEASURES**

The primary outcome measures will be the mean NRS pain scores and proportion of women with inadequate cervical cytology smears while the secondary outcome measures will be the pattern of Pap smear results and proportion of women willing to come for repeat testing.

4.12 **PLANNED HANDLING OF RESULTS**

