**TABLE 4: WILLINGNESS TO COME FOR REPEAT TESTING**

| Willingness to come for repeat testing | ALL | GEL | NO GEL | P VALUE |
| --- | --- | --- | --- | --- |
| YES |  |  |  |  |
| NO |  |  |  |  |

FIGURE 1. NUMERICAL RATING SCALE FOR PAIN

4.13 **STRENGTH AND LIMITATIONS OF THE STUDY**

This study is the first of its kind in a low income country like Nigeria, The limitation is that only one type of water- based lubricant will be used so results may not be applied to other kinds of lubricants. Perception of pain is complex and multifactorial. Cultural and genetic factors can affect these results in different populations.

Pap smear collection is provider technique dependent. Even though the researcher and research assistants will all be senior resident doctors with same level of training and experience, there still may be chances of inter provider differences. Except for the histopathologist, the researcher, research assistants and patients will be aware of the intervention assignment because given the nature of the intervention technique, blinding of participants and researcher/ research assistants will be difficult.

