**APPENDIX 2**

**RESEARCH PROFORMA**

**EFFECTS OF SPECULUM LUBRICATION ON CERVICAL SMEARS FOR CERVICAL CANCER SCREENING: A DOUBLE-BLIND RANDOMIZED CONTROLLED TRIAL**

Please do fill the parameters below. Tick [X] where appropriate.

Code No………Folder Number………………Date of Enrolment……………

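### The abstract and the proforma title call the trial double-blind, but section 4.13 says women and operators will know the arm, so the self-reported outcomes are open to expectation bias

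*Protocol*

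**What the plan says.** The protocol describes blinding in four places.

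- **Abstract, Strengths and Limitations:** "The histopathologist and the study participants will be blinded hence double-blind". The label is derived from the blinding of these two parties.
- **Appendix 2, Research Proforma, title:** "A DOUBLE-BLIND RANDOMIZED CONTROLLED TRIAL". Only the label appears here; the proforma does not say who is blinded.
- **Section 4.10, laboratory paragraph:** "The histopathologist will not be aware of the intervention arm (group of patients) to which the smears to be analysed belong". No other party is named as masked.
- **Section 4.13:** "Except for the histopathologist, the researcher, research assistants and patients will be aware of the intervention assignment". The reason given is that, with this kind of intervention, "blinding of participants and researcher/ research assistants will be difficult".

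Section 4.11 makes the mean pain score and the proportion of inadequate smears the primary outcomes, and willingness to return a secondary one. Under section 4.10 the woman rates her discomfort from 0 to 10 at the end of the procedure and says whether she would come again. Under sections 4.8 and 4.10 the researcher and five research assistants both carry out the procedure and collect the data.

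**The concern.** The abstract and section 4.13 make opposite statements about the same women, and both are current text. A reader of the abstract or the proforma would take the pain score to have been reported without knowledge of the arm. A reader of section 4.13 would know that it was not.

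This matters because two of the outcomes are the woman's own report. Chapter One says openly that lubrication should be used to lessen pain. If a woman knows that she did or did not receive gel, and the person recording her answer knows it too, a shift in reporting cannot be told apart from a real reduction in pain. An analysis plan cannot repair this, because who is masked is settled by design and conduct. Section 4.13 admits the lack of blinding but does not say what it does to the pain or willingness results.

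**Working it through.** **1. The passages side by side**

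| Party | Abstract | Sections 4.9 and 4.10 | Section 4.13 |
| --- | --- | --- | --- |
| Histopathologist | Blinded | Blinded | Blinded |
| Participants | Blinded | No masking described | Aware |
| Researcher and assistants | Not stated | No masking described; they use a gelled or a dry speculum | Aware |

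The participants' row conflicts directly. The methods side with section 4.13: they provide sealed envelopes, a gelled or dry speculum and a masked reader of the smears. They contain no step that withholds the arm from the woman, screens the preparation of the speculum or supplies a sham. Carried out as written, the trial masks the histopathologist only.

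**2. Which outcomes are exposed**

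- Pain (primary): reported by the woman and collected by unmasked staff. Exposed.
- Willingness to return (secondary): the same. Exposed.
- Smear adequacy (primary) and the pattern of smear results (secondary): read by a masked histopathologist. Not exposed to this reporting bias, although the operators who take the smear are unmasked.

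**3. An illustration of what a reporting shift could do**

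Inputs:

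- n = 60 per arm. Section 4.3 gives 4669 / (1 + 4669/60) = 4669 / 78.82 = 59.2, taken as 60. The figure reproduces and is used here only as the analysed number; whether that step is sound is a separate question.
- Two-sided 0.05, from section 4.12.1 and the 1.96 in section 4.3.
- SD. The protocol gives none for its own pain score. Section 2.5 reports 1.57 and 1.71 for a visual analogue score at speculum introduction in a gynae-oncology trial. Their mean is (1.57 + 1.71) / 2 = 1.64. This is an assumption, and 2.5 is used as a wider alternative.
- True effect: none (assumed).
- Reporting shift b of 0.3 or 0.5 points (assumed; the documents give no value).

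Formula: SE = SD × √(2/60), and P(significant) ≈ Φ(b/SE − 1.96) + Φ(−b/SE − 1.96). The t column uses the exact noncentral t with 118 degrees of freedom.

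| SD | SE | b | b/SE | P, normal | P, t-test |
| --- | --- | --- | --- | --- | --- |
| 1.64 | 0.299 | 0.3 | 1.00 | 0.17 | 0.17 |
| 1.64 | 0.299 | 0.5 | 1.67 | 0.39 | 0.38 |
| 2.5 | 0.456 | 0.3 | 0.66 | 0.10 | 0.10 |
| 2.5 | 0.456 | 0.5 | 1.10 | 0.20 | 0.19 |

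Without a shift the figure is 0.05. None of this alters the protocol's sample size.

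**The case against.** The strongest reply is that the protocol already discloses the position. Section 4.13 lists the lack of blinding as a limitation, and section 4.10 names only the histopathologist as masked. The body of the methods is therefore consistent, and the abstract sentence and the proforma title are the outliers. That is fair, and it makes the repair easy. It does not remove the contradiction, and section 4.13 still does not name the consequence for pain and willingness. The consent form is not in the text available for review, so what women are told is unknown; it could not make the abstract and section 4.13 agree.

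Four stronger readings are tempting, and the documents do not support them.

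- **That the protocol's own review refutes the claimed difficulty of masking.** Section 2.3 cites a trial in which "The women were not aware of their intervention arm placement". That trial compared gel with water on a plastic speculum, so both arms were wet. This trial compares gel with a dry metal speculum. The cited trial shows that the arm can be withheld with a moistened comparator; it does not show that masking against a dry speculum is easy.
- **That the expected effect is so small that modest bias would account for it.** The cited differences include 0.7 (2.3 − 1.6) and 1.0 (4.0 − 3.0), but also 1.33 (5.28 − 3.95) and a pooled 1.52 at dilatation. One cited trial found no significant difference in discomfort (p = 0.69). The range is wide, and the assumed shifts should not be measured against its lower end alone.
- **That unmasked operators can foresee allocations.** Section 4.9 fixes "randomly permuted blocks (blocks of 4, allocation ratio 1:1". Over the 6 possible blocks, 8 of 24 positions (33%) follow from the earlier ones: two each in the two blocks that begin with a matching pair, one each in the other four. The arithmetic is right but is a ceiling. It requires an operator to know the block size and every earlier allocation in the block, across six data collectors, while an independent person keeps and opens sealed opaque envelopes. It is a separate, secondary point about concealment.
- **That the proforma itself asserts that participants are blinded.** It carries the label only.

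**Conclusion.** The point stands as a direct contradiction that must be corrected. The abstract says that women are blinded, section 4.13 says that they are aware of their arm, and the methods describe masking of the histopathologist only. On the methods as written, the double-blind label is false, and pain and willingness are open to expectation bias. Smear adequacy keeps its masked reading.

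The contradiction rests on the text alone and needs no assumption. The size of any bias is not known. The figures of about 17% and 38% for shifts of 0.3 and 0.5 points depend on an assumed shift, an assumed SD of about 1.64 borrowed from another scale and population, and no true effect; with SD 2.5 they fall to about 10% and 20%. They show that a small reporting shift could matter at this sample size. They do not estimate this trial's false-positive rate, and a reader should not infer from them that a favourable pain result would be spurious.

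**What to change.** State one blinding status in the abstract, section 4.10, section 4.13 and the proforma title. There are two ways to do this.

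1. **Women remain unmasked.** Replace double-blind with histopathologist-blind in the abstract and the proforma title, delete the statement that participants are blinded, and add a sentence to section 4.13 that the pain and willingness results are open to expectation bias.
2. **Women are to be masked.** Describe in section 4.10 how this is done (for example, the arm not disclosed and the speculum prepared out of sight), correct section 4.13 to match, and acknowledge that masking gel against a dry speculum may be imperfect because some women may feel the difference.

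The first option costs only wording. The second adds a small change to clinic routine. Neither needs extra staff or alters the sample size. Randomly varying block sizes would be an optional, separate improvement, made as a setting when the independent person generates the sequence.

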**CHAPTER ONE**

**INTRODUCTION**

Cancer of the cervix ranks fourth in the list of the most prevalent malignancies in females with a projected 570 000 incidence in 2018. ^1^ It represents 6.6 per cent of all gynaecological carcinomas and is responsible for 7.5 per cent of all female malignancy mortality worlwide.^1^ Out of the 311 000 cases of mortality estimated from carcinoma of the cervix yearly, greater than 85% of these deaths happen in areas that are less developed.^1^

Cervical carcinoma is the predominant gynaecological malignancy occurring in females of sub-Saharan African region ^4^ with a projected 70,722 incidence annually,^5^ while it comes second in Nigeria with breast cancer topping the list of malignancies in women. ^6,7,8^ Previous studies have shown that 53.1 million females older than 15 years have increased chances of having carcinoma of the cervix in Nigeria.^9^ There are 14,943 people diagnosed yearly in Nigeria with 10,403 deaths and an incidence of 15.5 per 100,000 women. ^9^

Introducing screening for cancer of the cervix and improving its uptake in developing countries is a key factor in decreasing burdens due to deaths from malignancy of the cervix. The usage of screening programs can be improved via increasing sensitization on factors that increase chances of having carcinoma of the cervix which include many sex partners, early coitarche, multiparity, HPV infections, early pregnancy, extensive use of oral contraceptives and HIV infections.^10^

Screening methods for cancer of the cervix include the conventional Papanicolaou test, colposcopy, Visual Inspection of the cervix with Lugol’s iodine and Acetic acid and Human papilloma virus testing .^11^ Presently there are 3 kinds of vaccines available against HPV infection namely Cervarix, Gardasil 4, and Gardasil 9. ^12,13^

In high income countries, there are well structured programs which enable vaccination of girls against HPV and regular screening of women resulting in remarkable decrease in the development and complications of carcinoma of the cervix.^14,15,16^ Screening helps to achieve early identification and intervention which prevents up to 80% of cervical malignancies in high income countries,^14,15,16^ whereas in poor income countries, there is poor access to vaccination and testing resulting in diagnosis of cervical cancer mainly in advanced stages.^2,3^ In addition, these countries lack access to facilities required for the management of such advanced stage diseases giving rise to a greater death rate from malignancy of the cervix in poor countries.^2,3^

In as much as efforts are been made to improve vaccinations for HPV in order to prevent carcinoma of the cervix, early identification of premalignant lesions of the cervix through cervical Papanicolaou smear cytology screening remains a key factor for achieving a decline in the development and complications of carcinoma of the cervix in poor income countries where vaccination for Human Papilloma Virus services is limited.^18^

The Papanicolaou test is a well-recognized, efficient and reliable tool employed in early identification of premalignant lesions of the cervix resulting in substantial decrease in disease burden of carcinoma of the cervix.^19^ It is cost-effective and the technique is simple. Despite this, the uptake of Papanicolaou smear in our environment remains poor.^2^ Pain and discomfort associated with examination of the vagina can discourage women from assessing regular test.^20^ Other factors that may hinder compliance include lack of awareness, cost implication, anxiety and cultural beliefs.^40^

Insertion of speculum for examination of vagina is an important factor responsible for non- compliance to regular screening and repeat testing for carcinoma of the cervix because of the embarrassment, anxiety, pain and discomfort associated with it.^21^  In Australia, a research seeking to find out the attitude of women concerning self-insertion compared to physician insertion of the speculum showed that 91% of the study population will prefer to insert the speculum by themselves rather than a physician doing it because of the embarrassment and discomfort associated with it. ^22^

During intercourse, lubrication is physiologically essential for easy penetration of the vagina and absence of optimal lubrication results in dyspareunia. So we cannot justify inserting without lubrication a rigid instrument like a speculum into the vagina. It is the duty of gynaecologists to alleviate the pain and discomfort encountered in vaginal examinations with speculum to prevent the unfavourable effects of women refusing vaginal examinations due to pain. Speculum lubrication should be employed to minimize discomfort and pain during vaginal examinations thereby ultimately increasing compliance for screening. However, applying lubricating gel on the vagina is not encouraged by gynaecologic literature, also students and resident doctors in training are advised against lubricating the speculum while collecting sample due to the worry that it may interfere with cytology results of cervical smears often leading to inadequacy.^17,19^ However there is paucity of convincing evidence to prove that using lubricating gel can prevent proper cytological analysis.^23,24,25^

To the researcher’s best knowledge, only few studies are published worldwide ^19,20,30, 33-39^ and none was done in this environment. The goal of this research work therefore is to find out if lubrication during speculum insertion has effects on the adequacy of cervical cytology smears and to determine if it decreases pain and discomfort in women undergoing cervical cancer screening by means of cervical smears and also compare the proportion of women willing to come for repeat cervical smears in the future.

**CHAPTER 2**

**LITERATURE REVIEW**

In this chapter, similar and related literature to this study were reviewed under the following sub-headings:

**Screening Options for Cancer of the Cervix**

**Options of speculum lubrication**

Water soluble lubricant gels

Topical analgesic containing lubricant gels

**Speculum lubrication and adequacy of cervical smears**

Studies on effects of lubrication on adequacy of cervical smears for cervical cancer screening.

**Speculum lubrication for cervical screening and pain perception**

Studies on pain perception following lubrication for cervical smear collection during cervical cancer screening

**Speculum lubrication for cervical smears and willingless for repeat cervical cancer screening**

**S**tudies on barriers affecting willingness for repeat cervical cancer screening

**Conclusion of literature review**

2.1 S**EARCH STRATEGY**

The following search engines were used: PubMed, Google scholar, Research gate, Medline and Cochrane library. The keywords for the search were Pap smear, Papanicolaou smear, cervical cytology, speculum lubrication, gel, KY jelly, and Pap smear result adequacy. Advanced PubMed search yielded the following search terms: (Effect[All Fields] AND lubricating[All Fields] AND gel[All Fields] AND ("patient comfort"[MeSH Terms] OR ("patient"[All Fields] AND "comfort"[All Fields]) OR "patient comfort"[All Fields]) AND ("vagina"[MeSH Terms] OR "vagina"[All Fields] OR "vaginal"[All Fields]) AND ("surgical instruments"[MeSH Terms] OR ("surgical"[All Fields] AND "instruments"[All Fields]) OR "surgical instruments"[All Fields] OR "speculum"[All Fields]) AND ("physical examination"[MeSH Terms] OR ("physical"[All Fields] AND "examination"[All Fields]) OR "physical examination"[All Fields] OR "examination"[All Fields])) AND ("randomized controlled trial"[Publication Type] OR "randomized controlled trials as topic"[MeSH Terms] OR "randomized controlled trial"[All Fields] OR "randomized controlled trial"[All Fields])

Additional references not identified by the initial search were retrieved from the reference section of the articles gotten from the search.

